### Academic outcomes

#### On-task behavior

Time spent on-task during English lessons will be observed using momentary time sampling, reported as a percentage of time, categorized as “on-task” (consisted of “actively engaged” or “passively engaged”), and “off-task” [66]. Active engagement refers to the time a child is actively engaged in an academic activity (e.g., reading, writing, or performing the designated task), rather than passive engagement (i.e., looking at an appropriate target (e.g., the teacher) but not actively engaged in the activity). Off-task behavior is related to behavior not associated with the task (e.g., off-task motor behavior, walking around the class, off-task verbal behavior, chatting, or off-task passive behavior, staring in the class [34, 67]. This observational tool has been adapted from the “Behavior Observation of students in schools” and the “Applied Behavior Analysis for Teachers” [66, 68]. Twelve students (6 boys, 6 girls) will be observed during their English lessons (e.g., 9:00–11:00 am) in 15 s intervals on a rotational basis over a 30-min period in the allocated English time slot. Two lesson observations per school at each time point will be included. Two trained research assistants will observe simultaneously, after receiving a 2-h training focusing on identifying and classifying behavior into the appropriate categories, and a practice trial.

#### Academic achievement

The standardized test “Progressive Achievement Test (PAT)” will be administered in the classroom under 30-min of exam conditions, based on the Australian Curriculum for Education Research (ACER) recommendations [69]. This battery includes different assessments for written spelling (30 items) grammar and punctuation (35 items).

#### Executive function

Cognitive assessments will be measured using the National Institute of Health (NIH) Toolbox Assessment of Neurological and Behavioral Function for 7–17 years (www.nihtoolbox.org), installed on iPad devices [70]. This is a validated instrument for children between 3 and 15 year-old [71] and includes measures of attention, cognitive control, episodic and working memory, language, and processing speed.

Two measures of executive function (i.e., inhibition and cognitive control) will be selected: The Eriksen Flanker task examines the ability to selectively attend and respond to a target stimulus, while resisting interference input that competes with the target. Participants respond with their left or their right hand according to the direction of the central arrow of a multi-arrow display. The central arrow is flanked by arrows that are either congruent (i.e., point in the same direction as the central arrow, ➔ ➔ ➔ ➔ ➔) or incongruent (i.e., point in the other direction, 

). Congruent trials elicit faster and more accurate responses that incongruent trials [72, 73]. Four practice trials are presented prior to the assessment [74]. Twenty trials are conducted for ages > 8. The test takes approximately 3–5 min to administer.

The Dimensional Change Sort Test measures two dimensions of cognitive control: concept formation (i.e., the ability to identify and respond to a specific task-set) and cognitive flexibility (i.e., the ability to use feedback to switch between different task-sets). Participants are presented with stimuli that can be classified according to two dimensions (e.g., shape and colour). They are required to sort the stimuli using one dimension (e.g., trucks vs. cars) irrespective of colour. After a certain number of correct trials, they are required to change rules and sort the stimuli using the other dimension (e.g., red vs. blue pictures). Students are given three practice trials which are directly followed by the examination [74]. This test takes approximately 4–6 min to administer.

In both cognitive measures, scoring will be based on a combination of accuracy and reaction time [74]. Accuracy and reaction time are calculated via a 2-vector scoring method: each of these “vector” values range between 0 and 5, and the computed score that combines the vector scores ranges from 0 to 10. If participants’ accuracy levels are ≥80%, the final “total” computed score is equal to the accuracy score. If participants’ accuracy levels reach < 80%, the accuracy and reaction time score are combined [74].

The uncorrected standard score will be calculated for both cognitive measures, using a standard score metric (normative mean = 100, *SD* = 15). Participants’ overall level of cognitive functioning will be compared with the entire NIH toolbox U.S. representative normative sample, regardless of any demographic characteristics (e.g., age, gender). High scores indicate higher performance [74].

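### The printed scoring rule for both executive-function tests contradicts its own 0 to 10 range and scale direction; its two branches appear to be reversed

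*Protocol article*

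**What the plan says.** The Executive function section under Measures names two tests, the Flanker task and the Dimensional Change Sort Test, and gives one scoring rule for both: "In both cognitive measures, scoring will be based on a combination of accuracy and reaction time".

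The rule has these parts:

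- Component range: "each of these “vector” values range between 0 and 5".
- Total range: "the computed score that combines the vector scores ranges from 0 to 10".
- Upper branch, at accuracy of 80% or more: the "computed score is equal to the accuracy score".
- Lower branch: "If participants’ accuracy levels reach < 80%, the accuracy and reaction time score are combined".

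The next paragraph says that the uncorrected standard score (normative mean 100, SD 15) will be calculated for both tests without regard to demographic characteristics, and closes with "High scores indicate higher performance". No other section restates or corrects the rule. Executive function is listed as a secondary outcome in the Abstract and in Aims and hypotheses.

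**The concern.** The two branches run against the rest of the description. Children who answer most items correctly get no credit for speed, and children who make many errors do. The more accurate group is therefore capped at half of the stated maximum, while the less accurate group can pass that cap.

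At stake are the only two executive-function tests that the article names. The hypothesis is that the intervention group improves on all measures. Under the rule as printed, some genuine gains in accuracy would lower the score, and speed would carry no information for any child at or above 80%.

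**Working it through.** **Inputs, all from the Executive function section.** Accuracy component A and reaction-time component R, each 0 to 5; stated total range 0 to 10; threshold 80%; 20 Flanker trials for children older than 8.

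**Rule as printed.** Total = A if accuracy ≥ 80%; total = A + R if accuracy < 80%.

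**Step 1: can the stated range be reproduced?** No. At or above 80% the total is A, so it is at most 5. A total of 10 needs A = 5 and R = 5 in a child below 80%. That is impossible unless the accuracy component already reaches its maximum below 80%, which nothing in the article suggests.

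**Step 2: does a higher total mean better performance?** Take a child below 80% with any A > 0 and R = 5. The total is A + 5, which is more than 5. A child with perfect accuracy and the same R = 5 scores 5. The second child is more accurate and equally fast, yet scores lower. This uses only the 0 to 5 ranges.

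**Step 3: worked sizes.** These need an assumption that the article does not state: A = 5 × proportion correct.

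| Accuracy | A | R | Total as printed | Total with branches swapped |
|---|---|---|---|---|
| 75% (15/20) | 3.75 | 3 | 3.75 + 3 = 6.75 | 3.75 |
| 75% (15/20) | 3.75 | 5 | 3.75 + 5 = 8.75 | 3.75 |
| 80% (16/20) | 4.00 | 3 | 4.00 | 4.00 + 3 = 7.00 |
| 85% (17/20) | 4.25 | 3 | 4.25 | 4.25 + 3 = 7.25 |
| 100% (20/20) | 5.00 | 5 | 5.00 | 5.00 + 5 = 10.00 |

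As printed, everyone at or above 80% falls between 4 and 5. Children below 80% range from 0 to 8.75 on 20 trials.

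**Step 4: when does crossing 80% lower the score?** The total goes from A₁ + R to A₂, so it falls exactly when R > A₂ − A₁. From 75% to 85%, A₂ − A₁ = 4.25 − 3.75 = 0.5.

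- With R = 3, the total moves from 6.75 to 4.25, a fall of 2.5.
- With R = 0.4, it moves from 3.75 + 0.4 = 4.15 to 4.25, a small rise.

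**Step 5: does swapping repair it?** With total = A below 80% and A + R at or above it, the range is 0 to 10: 0 to 3.75 below the threshold on 20 trials, and 4 to 10 at or above it. The order is also right. If A never falls as accuracy rises and R ≥ 0, a child at least as good on both components never scores lower. This ordering result does not need proportionality.

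An enumeration over 20 trials and R in steps of 0.25 compared ordered pairs in which one performer is at least as good on both components and better on one. As printed, 4,920 of 52,920 pairs (9.3%) score the better performer lower. With the branches swapped, none do, whichever branch takes exactly 80%. The 9.3% is a share of grid points and says nothing about the share of children.

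**The case against.** The strongest reply is that this is a misdescription of an existing instrument and not an analysis rule for the trial. The tests are run from the NIH Toolbox on iPads, the scoring method is described in the present tense with a citation, and the reported value is a standard score referenced to the Toolbox norms. Nothing says that staff will apply the 80% rule by hand. This stands as far as it goes: damage to the data is possible but not shown. The article does not say that the score comes from the software either, so the reply does not close the question.

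A second reply is that the sentence on direction belongs to the standard score and not to the 0 to 10 total. That is correct, and it makes that half of the contradiction indirect. However, the uncorrected score ignores age and sex. If the conversion to mean 100 and SD 15 is order-preserving, it carries any misordering of the totals with it. The conflict with the 0 to 10 range does not depend on this sentence.

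A reader might infer that any real improvement past 80% would be recorded as a decline, or that the executive-function results will be biased. The documents support neither. The fall occurs only when the lost reaction-time score exceeds the accuracy gain, and bias arises only if the printed rule is actually used. The article also gives no distribution of accuracy or reaction-time scores, so the effect on a group difference cannot be sized.

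**Conclusion.** The scoring rule is wrong as printed. The cap of 5 at or above 80% follows directly from the stated component ranges. It cannot be reconciled with a 0 to 10 total on which higher is better. Because one swap resolves both conflicts, reversed branches are the natural explanation, although the article alone cannot confirm what the cited source says.

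The consequence is conditional. If the rule is applied as printed, reaction-time information is lost for every child at or above 80%. Some children who cross the threshold score lower, by 2.5 points in the example from 75% to 85%, which rests on the proportional-accuracy assumption. The estimated effect on executive function could then be attenuated or reversed. If the software produces the score, the error is confined to the text, where it could still mislead anyone who rescores or replicates the tests. The primary physical-activity outcome is not touched in either case.

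**What to change.** 1. Swap the two conditions: accuracy alone below the threshold, accuracy plus reaction time at or above it.
2. Before publishing the correction, confirm the rule against the scoring source that the article cites (reference 74), including which branch takes a child at exactly 80%.
3. State that the analysed value is the software-generated uncorrected standard score and is not rederived by hand. If that is not so, describe how it is derived.
4. If any scores were computed by hand from the printed rule, recheck them before analysis.

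The cost is a correction to two sentences, one sentence on the source of the score, and a check of any hand-scored data. The design, the sample size and the analysis model do not change.

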### Process evaluation

The feasibility of the TWM-E program will be assessed using a range of measures including adherence, as well as teachers’ and students’ satisfaction. The following aspects of intervention implementation will be evaluated [75]: (i) *Fidelity and quality:* we will conduct three lesson observations per teacher during the program period using a semi-structured observation checklist (Table 3), (ii) *Responsiveness:* teachers’ evaluation of the TWM-E workshop, resources and their own lessons, and (iii) *Adaptation:* teachers’ modifications of TWM-E program resources (Additional file 1).

**Table 3 Tab3:** Evaluation checklist (Fidelity check)

Date:	Start Time:	Finish Time:				
English content						
Physical Activity						
(*Please circle and provide comments)*		*(1 = Not at all true* to *5 = Very true)*				
English concepts	i) Key English concepts were reinforced throughout the movement-based activity	1	2	3	4	5
	ii) Movement aided and promoted learning	1	2	3	4	5
	iii) Students were given feedback to support their English knowledge and understanding	1	2	3	4	5
Activity levels	i) Transitions were managed smoothly	1	2	3	4	5
	ii) Students assisted in the set-up and collection of equipment	1	2	3	4	5
	iii) Equipment used promoted physical activity	1	2	3	4	5
Engagement	i) Students were engaged by the activities taught	1	2	3	4	5
	ii) Students remained on-task throughout the lesson	1	2	3	4	5
	iii) Students enjoyed the movement-based English lesson	1	2	3	4	5
	Comments:					

Adherence (how many teachers completed program components): During the intervention period, teachers will be provided with weekly support, including advice and strategies by the research team during Weeks 1, 3, and 5 of the intervention. The lessons will also be observed during Weeks 2, 4 and 6, focusing on physically active English concepts (*n* = 3), activity levels (*n* = 3), and students’ engagement (*n* = 3). During the lesson observations, components of the workshop regarding English content and physical activity (i.e., engagement and activity levels) that will be adopted and adapted to the classes will be assessed through an evaluation checklist (see Table 3).

Teacher satisfaction: After the completion of the professional learning day, teachers will respond to the questionnaire assessing their perceptions on the skills acquired from the training, satisfaction and quality of the training, and their confidence to deliver physically active English lessons (Additional file 1). Teachers’ responses will be recorded answering on a 5-point Likert scale ranging from 1, ‘strongly disagree’, to 5, ‘strongly agree’. They will also have the opportunity through an open-ended response to provide the research team suggestions for improving the workshop and/or the program.

Teacher and student satisfaction: At the end of the 6-week intervention, students will complete an anonymous evaluation questionnaire of their perceptions of physically active English lessons both on enjoyment and perceived learning (Additional file 1). Responses will be ranked on a 5-point Likert scale ranging from 1, ‘strongly disagree’, to 5, ‘strongly agree’. Finally, at the end of the program, teachers and students will be invited to participate in semi-structured interviews (teachers) and focus groups (students) regarding their perceptions of the program (i.e., nature and quality of English lessons prior to and after the program, whether the TWM-E approach influenced their perceptions related to English and physical activity promotion; See Additional file 1). These measures will be adapted from the previously developed evaluation tools from the TWM program [76].

### Statistical analyses

Primary and secondary outcomes will be analyzed through linear mixed models, as they are robust to the biases of missing data and provide appropriate balance of Type 1 and Type 2 errors [77, 78]. Taking into account the hierarchical structure of the data in educational research (e.g., students nested within classes and schools), multilevel modelling analyses can be linked to several predictor variables at the individual level (e.g., students) and at a group levels (e.g., classrooms, schools [79, 80]). In this study, the models will be specified to adjust for the clustered nature of the data (i.e., class level was included as a random intercept) including all randomized participants in the analysis. Previous studies have shown that school-level clustering is negligible after accounting for clustering at the class level [81]. Analyses will be conducted using SPSS (version 22) and alpha levels will be set at *p* > 0.05. Data will be analyzed according to intention-to-treat principles. Qualitative data from teachers and students semi-structured interviews will be processed using a standard general inductive approach to qualitative analysis [82, 83]. Data will be transcribed verbatim, and then will be coded using thematic analysis.

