**Methods:**

Grade 3–4 children from 10 public schools in New South Wales, Australia will be randomly allocated to intervention (*n* = 5) or control (*n* = 5) groups. All teachers will receive 1-day workshop of registered professional learning and a TWM-E equipment pack (e.g., chalk, lettered bean bags). Intervention schools will be asked to adapt their English lessons to embed movement-based learning in their daily program for three 40-min lessons per week, over a six-week period. The primary outcome is children’s physical activity levels across the school day (measured using accelerometry). Secondary outcomes are children’s on-task behavior during English lessons, academic achievement in English, and executive function. A detailed process evaluation will be undertaken including questionnaires, fidelity checks, and teacher and student interviews.

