The design, conduct, and reporting of the TWM-E program will adhere to the Consolidation Standards of Reporting Trials (CONSORT) guidelines and the extension for cluster RCTs [49]. Participating schools will be stratified and pairs of schools will be matched according to their enrolment size and demographics (e.g., literacy program, socio-economic status and location), using the index of community socio-educational advantage (ICSEA). The ICSEA value includes data and information regarding family background (e.g., parental occupation, school/ non-school education achieved) provided to schools directly by families. Following baseline assessments, an independent researcher not involved in the project will use a random number producing algorithm to randomly assign each pair of matched schools to either control or the treatment condition. This method will ensure the same likelihood of allocation into one of the two study arms for all schools. Figure 1 shows the flow of participants. Schools in the waitlist control arm will continue with usual practice, which may include some schools pursuing other physical activity promotion initiatives. No restrictions will be made regarding schools’ participation in such programs, but they will be asked to provide details of their involvement. However, during recruitment, schools that are currently participating in physical activity programs run by the University (e.g., iPLAY [50]) will not be targeted for inclusion.

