### Sample size calculation

Power analysis using procedures appropriate for a cluster RCT study design [51] were conducted to determine the sample size required to detect changes in the primary outcome of accelerometer-determined physical activity counts per minute (CPM). Calculations assumed baseline to post-test correlation scores of *r* = 0.30 and were based on 80% power and alpha level 0.05. Based on the reported physical activity effects (i.e., *SD* change = 200 CPM) after six weeks of the TWM in Maths study pilot study, and a conservative intra-class correlation coefficient (ICC = 0.15), a study sample of *N* = 200 with 8 clusters (i.e., schools) of 25 students would provide adequate power to detect a between group difference of 200 CPM across the school day [34, 52].

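### Schools are randomised, but the analysis model has only a class random intercept; if schools contribute several classes and school variance remains, type I error can exceed 5%

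*Protocol article*

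**What the plan says.** The abstract (Methods) states the design: "Grade 3–4 children from 10 public schools in New South Wales, Australia will be randomly allocated to intervention" or control, five schools to each. Under Participants, "pairs of schools will be matched according to their enrolment size and demographics", and after baseline an independent researcher is to "randomly assign each pair of matched schools to either control or the treatment condition". Taken literally, that phrase allocates whole pairs, which cannot produce five against five. I read it as one school of each pair going to each arm.

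The Sample size calculation also works at school level. It assumes an intraclass correlation (ICC) of 0.15 and "8 clusters (i.e., schools) of 25 students".

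The Statistical analyses section describes the data as "students nested within classes and schools", but the only random term it specifies for the primary and secondary outcomes is class: "class level was included as a random intercept". The reason given is "Previous studies have shown that school-level clustering is negligible after accounting for clustering at the class level". No school or pair term is named.

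**The concern.** Only ten units are randomised. Children in different classes of one school share its allocation and whatever else is common to that school. A class-only model treats those classes as if each had been allocated independently. With c classes per school it tests treatment on about 10c − 2 degrees of freedom (18 for c = 2, 28 for c = 3), where the design gives 8 before pairing. Any between-school variance not captured elsewhere then makes chance differences between arms look more precise than they are.

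The primary outcome makes this a practical worry. Activity is recorded across the whole school day, so timetable, breaks and playground are common to all classes of a school. Control schools may also run other activity programmes, which is another school-level influence. Every primary and secondary p-value and interval comes from this model. The omission is a stated rule with a stated reason, so it is not a detail merely left to a later analysis plan.

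**Working it through.** **1. The plan's own figure, with school as the cluster.** Inputs from the Sample size calculation: difference 200 counts per minute (CPM), SD 200 CPM, r = 0.30, ICC 0.15, 25 students per school, 80% power, alpha 0.05 (two-sided assumed).

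- Design effect: 1 + (25 − 1) × 0.15 = 4.6.
- Change-score SD: 200 × √(2 × (1 − 0.30)) = 236.6.
- Unclustered n per arm: 2 × 7.849 × (236.6/200)² = 21.98.
- Clustered total: 2 × 21.98 × 4.6 = 202.2, or 8.09 schools of 25.

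This matches N = 200 in 8 schools. It requires reading 200 CPM as the SD at one time point, although the text labels it an SD of change; that does not affect the present point. The planned size therefore carries clustering at school level.

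**2. How far the class-only standard error can be off.** Let vs be the school variance not absorbed elsewhere, vk the variance of a class mean within a school (class variance plus residual variance divided by class size), and c the classes per school, with five schools per arm.

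- True variance of an arm mean: (vs + vk/c)/5.
- Variance the class-only model expects: [vs + vk − vs(c − 1)/(5c − 1)]/(5c).

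Illustration, with all inputs assumed: vs = 0.15, class variance 0.05, two classes of 25.

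- vk = 0.05 + 0.80/25 = 0.082.
- True: (0.15 + 0.041)/5 = 0.0382.
- Model: (0.232 − 0.15/9)/10 = 0.0215.
- Ratio of standard errors: √(0.0382/0.0215) = 1.33.

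**3. Type I error by simulation.** 40,000 null trials per scenario, five pairs of schools, total ICC held at 0.15 and split between school and class. With balanced data the class-intercept model is equivalent to a t-test on class means. Matching absorbs nothing in this table:

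| Residual school ICC | 1 class of 25 | 2 classes of 12 | 2 of 25 | 3 of 8 | 3 of 25 |
|---|---|---|---|---|---|
| 0 | 0.051 | 0.049 | 0.051 | 0.051 | 0.050 |
| 0.02 | 0.051 | 0.060 | 0.062 | 0.070 | 0.078 |
| 0.05 | 0.051 | 0.079 | 0.085 | 0.097 | 0.121 |
| 0.10 | 0.049 | 0.110 | 0.125 | 0.152 | 0.189 |
| 0.15 | 0.051 | 0.144 | 0.168 | 0.200 | 0.258 |

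A second simulation without pairing (100,000 null trials per scenario) agrees: 0.126–0.167 with two classes and 0.212–0.254 with three at school ICC 0.15; 0.078–0.115 at 0.05; 0.060–0.075 at 0.02.

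**4. The effect of matching.** The same class-only test, when part of the school variance is shared within pairs, over school ICC 0.02 to 0.15:

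- Half shared: 0.049–0.066 (2 × 12) and 0.057–0.105 (3 × 8).
- 80% shared: 0.026–0.046 (2 × 12) and 0.043–0.047 (3 × 8).
- All shared: 0.005–0.041 (2 × 12).

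**5. Analyses at school level.** School-pair differences on 4 df gave 0.048–0.052 in every scenario. The unpaired school-level test on 8 df gave about 0.05 when matching explains nothing and fell below when it explains something, for example 0.019 with two classes of 12, school ICC 0.15 and half shared.

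**The case against.** The strongest reply is that the documents do not show any inflation.

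- **Classes per school are not given.** The sample size has 25 students per school. The Intervention section counts three observations per school and the Process evaluation three per teacher, which agree only if there is one teacher per school. With one class per school, class and school are the same level and nothing is wrong. Against this, Grade 3 and Grade 4 teachers are invited, and the negligibility sentence has content only if class and school differ in at least some schools. Several classes per school is the likelier reading, but it remains an inference.
- **The choice is referenced.** The cited source cannot be checked here, so I do not say that it is wrong. It is still applied to every outcome, and ten schools could hardly confirm it.
- **The ICC of 0.15 is not school variance net of class.** It is one ICC, described as conservative, for clusters of 25. The row at 0.15 is therefore an upper scenario. Nor does the sample size flatly contradict the analysis: it does not separate school from class.
- **Baseline is measured.** Stable school differences would partly drop out of a baseline-adjusted or change analysis. The simulations use one time point, and the ICC that matters is the one left after adjustment, which is not given.

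A reader might infer that leaving out the matched pair adds to the inflation. It does the reverse: ignoring effective matching makes standard errors too large. A reader might also take the missing pair or matching covariates as an error in itself. The section lists no fixed effects at all, so that is mostly silence. What stands is the explicit exclusion of school.

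**Conclusion.** The concern holds conditionally. The unit of randomisation is excluded from the model by a stated rule whose only support is earlier studies. If schools supply more than one class and school variance remains after class, baseline and matching, standard errors are too small and type I error can exceed 5%. For two or three classes per school and no variance absorbed by matching, the size is about 6–8%, 8–12% and 13–26% at residual school ICCs of 0.02, 0.05 and 0.15. These rest on assumed class numbers and sizes, balanced data and a single time point.

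It would go too far to say that the false-positive rate does exceed 5%, or to quote one figure for it. Inflation is nil with one class per school or no residual school variance, and it disappears or reverses when matching absorbs most of that variance. The documents settle none of these conditions, so the analysis should not depend on them.

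**What to change.** In Statistical analyses:

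- Specify random intercepts for school and for class within school, and keep the school term even if its estimated variance is small.
- Test treatment with small-sample degrees of freedom based on the number of schools.
- Remove the negligibility justification.
- Reflect the matching, either with a pair term (or an analysis of school-pair differences, 4 df) or by adjusting for the socio-educational index (ICSEA) and enrolment size.

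The work is a change of wording and one or two more model terms. The statistical cost is wider intervals and some power. On the sample-size inputs in step 1 of the working, with ten schools of 25, the standard error is 236.6 × √(2 × 4.6/125) = 64.2 and the noncentrality 200/64.2 = 3.12. Power is then 0.779 on 8 df and about 0.65 on 4 df if matching gains nothing. Effective matching would recover part of that loss, so the choice between pair term and covariates should be made before the outcome data are seen.

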### Measures

Consenting students will be assessed at two time points using identical measures (baseline and 3-months). Trained research assistants will collect student level assessments, and where possible the same assessors will be used for both time points. Research assistants will be blinded to schools’ allocation to the conditions. More specifically, on-task behavior, followed by the cognitive assessments will be conducted by research staff on the same day at the same time for each time point (i.e., Monday, 9:00 am, baseline and posttest). To avoid participant burden, academic achievement tests will be administered by the classroom teachers on a different day using a standardized data collection protocol given to the teachers by the research team. Students’ demographic information characteristics will be collected at the end of the intervention.

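### A class random intercept is the only clustering term named; if both visits are modelled as outcomes, it cancels from the group-by-time effect, whose standard error then omits cluster-level variation in change

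*Protocol article*

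**What the plan says.** The Statistical analyses section gives the model family: "Primary and secondary outcomes will be analyzed through linear mixed models". It prefers these models for their behaviour under missing data and promises to fit them "including all randomized participants in the analysis". The adjustment for clustering is spelled out as "class level was included as a random intercept". The school level is left out on the ground that "Previous studies have shown that school-level clustering is negligible after accounting for clustering at the class level". No child-level term, repeated-measures covariance or class-by-time term is named. Nor does the section say whether the treatment effect is a group-by-time interaction or an arm effect on the post-test adjusted for baseline.

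The Measures section states that "Consenting students will be assessed at two time points using identical measures". Under Participants, the allocation step is to "randomly assign each pair of matched schools to either control or the treatment condition", so the school is the randomised unit. The Methods paragraph of the abstract gives 10 schools, 5 per arm.

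**The concern.** A random intercept that is constant over time describes how far a class sits above or below average at both visits. It says nothing about how much a class drifts between visits. If the treatment effect is the difference between arms in change, drift at class and school level is the error that matters, because whole schools are allocated. A model with only a class intercept then judges that effect against within-class variation alone. The clustering adjustment that the section promises would not reach the primary comparison.

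Some drift is to be expected. Baseline and post-test fall in different school terms. Accelerometers are worn for one school week per visit, so children measured together share that week's conditions. Intervention teachers design their own active lessons, and control schools may take up other activity initiatives without restriction. At stake are the p-value and confidence interval for the primary outcome.

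**Working it through.** **Inputs.** From Sample size calculation: ICC ρ = 0.15, baseline to post-test correlation r = 0.30, SD 200 CPM, difference 200 CPM, 80% power, alpha 0.05 (two-sided used here; sidedness is not stated), 8 schools of 25, N = 200. From the abstract: 5 schools per arm. Assumed for illustration: one class of m = 25 per school, so K = 5 clusters and n = 125 children per arm, and a between-visit correlation π of the cluster effect, which the article does not give.

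**The plan's own figure.** The design effect is 1 + (25 − 1) × 0.15 = 4.6. Treating 200 as the SD at one visit, the SD of change is 200 × √(2 × (1 − 0.30)) = 236.6. This gives 21.98 per arm before clustering, and 21.98 × 4.6 = 101.1 per arm, about 202 in total against the stated 200. The other two-sided variants do not match: SD 200 without r gives 146, and the baseline-adjusted factor √(1 − r²) gives 132. The stated N therefore fits a change-score calculation with the design effect applied to change.

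**What the intercept does in a two-visit model.** Write the outcome as fixed part + u(class) + e(child, visit). Subtracting a child's two values removes u. In balanced data the group-by-time estimate is the difference between arms in mean change, so the model assigns it

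- model variance = 4σ²e / n,

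with no class variance in it. If cluster effects correlate π between visits, the actual variance is

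- true variance = 200² × (2/K) × [2ρ(1 − π) + {2(1 − r) − 2ρ(1 − π)}/m].

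At π = 0.3: 0.4 × [0.21 + 1.19/25] = 0.10304, and 200 × √0.10304 = 64.2 CPM. The ICC of change is 0.21/1.4 = 0.15, which is the sample-size premise.

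**Results** (4,000 simulated trials per row; last column is t on 8 df):

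| π | True SE | Model SE, class intercept | Type I error | Type I error, child intercept added | Type I error, class-by-time |
|---|---|---|---|---|---|
| 1.0 | 29.9 | 32.9 | 0.034 | 0.051 | 0.052 |
| 0.8 | 42.6 | 33.2 | 0.128 | 0.170 | 0.048 |
| 0.5 | 56.6 | 33.5 | 0.248 | 0.305 | 0.056 |
| 0.3 | 64.2 | 33.7 | 0.306 | 0.372 | 0.050 |
| 0 | 74.2 | 34.0 | 0.376 | 0.447 | 0.048 |

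A hand check uses 2[1 − Φ(1.96 × model SE / true SE)]. At π = 0.3, 1.96 × 33.7/64.2 = 1.03, which gives 0.30. At π = 0.9 the true SE is 200 × √(0.4 × [0.03 + 1.37/25]) = 36.8, and the model SE lies between 32.9 and 33.2, which gives about 0.08. Separate simulations gave 2.8%, 8%, 11–12% and 24% at π = 1.0, 0.9, 0.8 and 0.5. With two classes of 12 per school and the ICC split between school and class, the figures were 3.5%, 7%, 10% and 19%.

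The variance ratio (64.2/29.9)² = 4.6 shows what is lost at π = 0.3: the design effect on which the trial was sized.

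**The same intercept in a baseline-adjusted model.** At π = 0.3, 300 mixed-model fits of post-test on baseline and arm with a class intercept gave a mean SE of 0.253 against an empirical SD of 0.252 (in SD units). Type I error was 0.07 with z and 0.04 with t on 8 df. In the same 300 data sets the group-by-time fit gave 0.27.

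**The case against.** The strongest answer is that the article never says the model is group-by-time. It names no time factor and no interaction. Linear mixed models are also fitted with one row per child, and the wish to include everyone randomised sits beside an ordinary intention-to-treat statement. Under the baseline-adjusted reading the class intercept does its job. The fixed part, the child covariance and the degrees of freedom may be in a full protocol or analysis plan that is not shown. A sample-size formula does not fix the analysis model.

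Much of this stands. A reader might infer that the primary p-value and interval are simply wrong, or that the standard error has no allowance for clustering under any reading. The documents do not support that, because the fixed effects are unstated and one compatible model is sound. A reader might also infer that the error always runs towards false positives. It does not: with perfectly stable cluster effects no allowance is needed, the model is slightly conservative, and adding a child intercept corrects it. Adjacent school terms and identical measures make fairly stable cluster effects possible.

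What does not stand is the suggestion that this is only omitted detail. The section states what the clustering adjustment is and argues against the next level up. Its missing-data rationale fits a two-visit model better than a post-test model, which drops children without a post-test. Omitting the school, the randomised unit, is a separate point and adds no weight here.

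**Conclusion.** The concern holds conditionally. If both visits are outcomes, which is the more natural reading but not a stated one, the named random structure does not carry cluster-level variation in change into the standard error of the treatment effect. The consequence ranges from slight conservatism (about 3%) to a type I error of 8% to 24% at between-visit cluster correlations from 0.9 to 0.5, and about 30% at the value implied by applying the protocol's own ICC to change. These figures rest on an assumed between-visit correlation, on one class of 25 per school and on balanced data; results were similar with 4 or 10 clusters per arm. If the model is post-test adjusted for baseline, the problem does not arise at class level. The section should be changed so that the choice is not left open.

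**What to change.** State the primary model in one or two sentences under Statistical analyses. Preferred: post-test value on arm and baseline value, one row per child, with a random intercept for class (and for school, as a separate matter) and small-sample degrees of freedom such as Satterthwaite. If both visits are to remain outcomes, add a child random effect together with class-by-time and school-by-time random effects. A child intercept alone is not enough when cluster effects vary between visits.

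No new data are needed. The costs are wider intervals wherever the class-intercept model would have understated the error and, for the post-test model, the loss of children without a post-test. The sentence on including everyone randomised would have to be reconciled with that loss.
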